## Abstract

**Background:**

Chronic low back pain is an expensive and difficult condition to treat. One of the interventions widely used by physiotherapists in the treatment of chronic non-specific low back pain is exercise therapy based upon the Pilates principles. Pilates exercises can be performed with or without specific equipment. These two types of Pilates exercises have never been compared on a high-quality randomised controlled trial.

**Methods/design:**

This randomised controlled trial with a blinded assessor will evaluate eighty six patients of both genders with chronic low back pain, aged between 18 and 60 years, from one Brazilian private physiotherapy clinic. The patients will be randomly allocated into two groups: Mat Group will perform the exercises on the ground while the Equipment-based Group will perform the Pilates method exercises on the following equipment: Cadillac, Reformer, Ladder Barrel, and Step Chair. The general and specific disability of the patient, kinesiophobia, pain intensity and global perceived effect will be evaluated by a blinded assessor before randomisation and at six weeks and six months after randomisation. In addition, the expectation of the participants and their confidence with the treatment will be evaluated before randomisation and after the first treatment session, respectively.

**Discussion:**

This will be the first study aiming to compare the effectiveness of Mat and Equipment-based Pilates exercises in patients with chronic non-specific low back pain. The results may help health-care professionals in clinical decision-making and could potentially reduce the treatment costs of this condition.

**Trial registration:**

Brazilian Registry of Clinical Trials RBR-7tyg5j

## Background

Chronic low back pain is a common musculoskeletal problem worldwide [1] with an unfavorable prognosis [2]. Back pain is the second most prevalent health condition in Brazil [3] and is associated with high costs [4]. The etiology of low back pain is still unknown, but it is believed to be multifactorial. Therefore, degenerative, mechanical and postural conditions can be associated with low back pain [5-7]. Exercise therapy has been considered by the current clinical practice guidelines [8,9] as an effective treatment for chronic low back pain.

Exercise based upon the Pilates principles have been extensively used as an intervention for patients with chronic low back pain [6-10]. These exercises can be performed with specific apparatus (Equipment-based Pilates) or without them (Mat Pilates) [11]. Eight basic principles are considered to be essential while performing this intervention: diaphragmatic breathing, control, concentration, centering, precision, flowing movements, strength, and relaxation [12]. Previous systematic reviews on the effectiveness of the Pilates exercises in patients with low back pain revealed conflicting results [13-15]. While one review concluded that Pilates are effective for pain [13], other concluded that Pilates are effective for pain and disability [15] and finally the most recent review concluded that Pilates exercises were not effective in the reduction of pain and disability [14]. However, the authors from these reviews stated that most of the available trials are typically small and with suboptimal quality [13-15]. These issues reinforce the need for more studies on the effectiveness of Pilates exercises in the treatment of patients with chronic low back pain. To our knowledge there is no study that compared the effects of Mat-Pilates against Equipment-based Pilates in patients with chronic low back pain. The objective of this randomised controlled trial will be to compare the effectiveness of Mat Pilates and Equipment-based Pilates in the treatment of chronic non-specific low back pain patients. This study is likely to provide important information on the effectiveness and costs of these treatments as Equipment-based Pilates is more expensive than Mat Pilates for both physiotherapists and patients.

## Methods/design

### Study design

This is a randomised controlled trial with a blinded assessor that aims to assess the effectiveness of Mat and Equipment-based Pilates exercises in patients with chronic non-specific low back pain. The study has been approved by the Research Ethics Committee of the Universidade Cidade de Sao Paulo (PP 13610106), and is funded by National Counsel of Technological and Scientific Development (CNPq), Brazil (479645/2011-6). All participants will sign a consent form to agree to participate in the study.

### Participants

Our final sample will be composed by 86 patients seeking care for chronic non-specific low back pain from a private outpatient physiotherapy department from the city of Campo Limpo Paulista, Brazil, with a duration of symptoms of at least three months and aged between 18 and 60 years. The contraindications for exercise will be assessed with the Physical Activity Readiness Questionnaire, which is recommended as the minimal standard for pre-participation assessment as it can identify through a positive response the participants who need prior medical evaluation and authorization [16]. The exclusion criteria will be regular Pilates practice, pregnancy, serious spinal pathologies (fractures, inflammatory disorders or tumours), serious neurological impairment, inability to speak or write in Portuguese, and physiotherapy treatment for non-specific chronic low back pain in the past six months [17,18].

### Sample calculation

A sample of 86 participants was determined by a sample size calculation designed to detect a clinically important difference of one point in the Pain Numerical Rating Scale (estimated standard deviation = 1.4 points), one point in the Patient-Specific Functional Scale (estimated standard deviation = 1.4 points), one point in the Global Perceived Effect Scale (estimated standard deviation = 1.3 points), and four points in the Roland-Morris Disability Questionnaire (estimated standard deviation = 4.9 points) across all time points. These between-group differences were chosen based upon minimally important differences for patients with low back pain [19]. The following specifications will be considered: α=0.05, statistical power of 80% and follow-up loss of up to 15%. A correlation of r=0.50 between the follow-up assessments within the outcome measurement was assumed in these calculations.

### Intervention

All participants will receive their treatments based upon the Pilates principles. In the first treatment session, they will be given basic instructions on the method and training to activate core strength, i.e. isometric contraction of the transversus abdominis, perineal, gluteal, and multifidus muscles at expiration during diaphragmatic breathing. This core strength activation is also known as “powerhouse” [5,11,12,17]. Sessions will last one hour and will be provided twice a week over a period of six weeks. All exercises will be modified so that they can be performed at three levels of difficulty: basic, intermediate, and advanced. Some basic exercises can be tailored for each patient. For example, the “hip opener” can be performed in a lower range of motion and without resistance if needed. Similarly, other exercises, such as the “roll up”, can be progressed by using additional resistance. In the cases where all adaptations where not useful, the exercise will be replaced by another with the same objective. The level of difficulty for each exercise will be determined according to individual needs and increased as the participants reduce postural compensation [17,20,21]. Additional file 1: Appendix 1 presents a complete description of both treatments.

### Procedures

Patients will be assessed by an outcome assessor who will be unaware of the patient's allocation. This assessor will determine the eligibility of the patients as well as will collect the outcomes of the study. Outcomes will be collected at baseline, six weeks and six months after randomisation. Due to the nature of the interventions it will not be possible to blind the participants as well as the physiotherapist.

A simple randomization schedule was performed using Microsoft Excel for Windows by an independent researcher who will not be involved in participant recruitment and assessments. After the initial assessment, the participants will be referred to the physiotherapist overseeing the intervention and will be randomly allocated to one of two groups using consecutively numbered sealed opaque envelopes. The envelopes will contain a sentence that will inform the participants of their group allocation: Mat Group or Equipment-based Group (Figure 1). The Mat Group will perform the exercises on the ground. The Equipment-based Group will perform the Pilates method exercises on the following equipment: Cadillac, Reformer, Ladder Barrel, and Step Chair.

**Figure 1 F1:**
[figure not shown]
Flow diagram of the study.

This trial commenced recruitment in October 2011 and the last follow up is expected to be performed in November 2012.

### Outcome measures

#### Primary outcomes

Pain intensity will be measured by the Pain Numerical Rating Scale [22] which is an 11-point numerical scale (ranging from zero to 10), in which zero represents “no pain” and 10 represents “pain as bad as could be”. The participants will be asked to classify their average pain over the last week.

Disability associated with low back pain will be measured by the Roland-Morris Disability Questionnaire [23]. This questionnaire consists of 24 yes/no questions (total score ranging from zero to 24) related to normal activities of daily living in which every affirmative answer represents one point. The final score is the sum of these points. Lower scores represent less disability.

#### Secondary outcomes

Global Impression of Recovery will be measured by the Global Perceived Effect Scale [24]. This scale compares the onset of symptoms to the last few days. It is an 11-point scale (ranging from −5 to +5) in which −5 is “vastly worse”, zero is “no change”, and +5 is “completely recovered”. Higher score means greater recovery from the condition.

Function will be measured by the Patient-Specific Functional Scale [25]. The participants will identify three important activities in which they are having difficulty or which they are unable to perform due to chronic low back pain at the time of the assessment. Additionally, the participants will indicate on an 11-point scale (ranging from zero to 10) how capable they feel of performing these activities, with zero meaning “unable to perform the activity” and 10 meaning “able to perform the activity at pre-injury level”. The total score is calculated by the average of these three activities and ranges from zero to 10, with higher scores representing greater specific functional ability.

Fear of movement will be measured by the Tampa Scale for Kinesiophobia [26], which is a 17-item questionnaire with likert-type scales ranging from 1 “strongly disagree”, 2 “partially disagree”, 3 “partially agree” and 4 “strongly agree”. The final score ranges from 17 to 68 points, with higher scores indicating a higher degree of kinesiophobia.

All instruments described above have been translated and cross-culturally adapted into Brazilian-Portuguese and their measurement properties have been tested. The measurement properties of the Brazilian-Portuguese versions of these instruments are very similar to the original versions in English [27-31] with good estimates of reproducibility, construct validity and responsiveness.

We will be also measure patients’ expectancy and credibility with treatment. Expectancy will be measured by the Numerical Scale of Expectancy for Improvement. This is a method of assessing a patient’s expectation of improvement after treatment on a scale ranging from zero to 10, where zero represents “no expectancy for improvement” and 10 represents “expectancy for the greatest possible improvement”. This scale will only be used prior to the randomisation. The Treatment Credibility Scale is composed of four questions that assess the participants’ degree of confidence that if their symptoms will improve and confidence in the proposed treatment. The score ranges from zero to six, with zero being “not at all confident” and six being “very confident”. It will only be used after the first treatment session in both groups [32]. This scale is being translated and cross-culturally adapted into Brazilian Portuguese by our research group.

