### Statistical analysis

Data will be double-entered. The statistical analysis will be performed on an intention-to-treat basis. The effects of the intervention on pain intensity, global impression of recovery, general and specific disability, and kinesiophobia will be calculated using linear mixed models [33], which will incorporate terms for treatment, time, and treatment by time interactions (these interaction terms are equivalent to the between-group differences adjusted for the baseline estimates). The level of significance will be set at α=0.05. The data will be analyzed using the SPSS 19 for Windows by a blinded statistician who will receive coded data.

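### Expectancy is scored before randomisation but is not among the stated terms of the outcome model; adding it, with its time interaction, would be a small and cheap gain in precision, not the repair of an error

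*Protocol article*

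**What the plan says.** All references are to the protocol article.

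- **Secondary outcomes.** Expectancy of improvement is rated from 0 to 10, at baseline only: "This scale will only be used prior to the randomisation". Treatment credibility is a separate scale, given once the first session is over and so after allocation.
- **Statistical analysis.** Pain, global impression of recovery, general and specific disability, and kinesiophobia are analysed with linear mixed models, "which will incorporate terms for treatment, time, and treatment by time interactions". The interaction terms are presented as the between-group differences adjusted for baseline. Neither expectancy nor credibility appears, and no other use of either score is given. The statistician works with coded groups.
- **Procedures.** Allocation is by simple randomisation. Outcomes are taken at baseline, six weeks and six months. On blinding: "Due to the nature of the interventions it will not be possible to blind the participants as well as the physiotherapist". The assessor is blinded: "Patients will be assessed by an outcome assessor who will be unaware of the patient's allocation".
- **Primary outcomes.** The patient rates pain: "The participants will be asked to classify their average pain over the last week". Roland-Morris is a yes/no questionnaire.

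**The concern.** Expectation of improvement could plausibly predict how a participant later rates pain, disability or recovery. If it does, a model without it carries that variance as noise. Simple randomisation has no stratification, so the arms of one realised trial may also differ somewhat in mean expectancy. Because the score is fixed before allocation, conditioning on it is legitimate and does not disturb the randomised comparison. The trial already bears the cost of collecting it. At stake is a little precision in the primary pain and disability contrasts.

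**Working it through.** **The plan's own figure.** The article gives no figure for expectancy. Its only related figure is the total of 86. For pain (difference 1, SD 1.4, two-sided 5% assumed, 80% power), n per arm = 2 × [1.4 × (1.960 + 0.842)]² / 1² = 30.8, so 31 per arm or 62 in all. Dividing by 0.85 for loss gives 73, or 74 with equal arms. The stated 86 is larger, on the safe side. That is a separate matter, and nothing below depends on it.

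**Inputs.** From Sample calculation: 86 patients (43 per arm if equal), pain SD 1.4, target one point, loss up to 15%, correlation 0.50 between follow-up assessments. Assumed, not in the article: correlation ρ of expectancy with change in outcome, 0.2 to 0.4.

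**Step 1, the right scale.** The treatment-by-time term compares changes from baseline. If the 0.50 also holds between baseline and follow-up, the variance of change is 2 × 1.4² × (1 − 0.50) = 1.96, so its SD is again 1.4. On that assumption 1.4 serves for the contrast.

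**Step 2, unadjusted standard error.** 1.4 × √(2/43) = 1.4 × 0.216 = 0.302 points.

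**Step 3, effect of adjustment.** Residual variance is multiplied by 1 − ρ² and the standard error by √(1 − ρ²). Power is for pain at 43 × 0.85 = 36.55 per arm.

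| ρ | Residual variance | SE (points) | Equivalent extra patients, 86/(1 − ρ²) − 86 | Power after 15% loss |
|---|---|---|---|---|
| 0 | 1.00 | 0.302 | 0 | 86.3% |
| 0.2 | 0.96 | 0.296 | 3.6 | 87.6% |
| 0.3 | 0.91 | 0.288 | 8.5 | 89.3% |
| 0.4 | 0.84 | 0.277 | 16.4 | 91.5% |

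A simulation of 4,000 trials with 43 per arm and ρ = 0.3 agrees: the empirical standard error fell from 0.303 to 0.289.

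**Step 4, why the gain may be smaller.** With equal SDs and the 0.50 correlation of step 1, the correlation of expectancy with change is its correlation with follow-up minus its correlation with baseline. If these are 0.3 and 0.2, ρ is 0.1 and the variance falls by 1%. If they are equal, nothing is gained.

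**Step 5, chance imbalance.** The SD of the difference in mean expectancy between arms is 0.216 SD units. A difference of 0.3 or more has probability 2 × [1 − Φ(0.3/0.216)] = 0.16. At exactly 0.3 the pain contrast shifts by ρ × 0.3 × 1.4 = 0.08 to 0.17 points. That is 0.3 to 0.6 of the standard error in step 2, which already allows for it.

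**Step 6, does it touch reporting bias?** The same simulation carried an assumed between-arm reporting bias of −0.50 points. The mean estimate was −0.50 without expectancy and −0.50 with it.

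**Step 7, form of the term.** A score measured once, entered as a main effect, shifts all of a patient's visits equally and cancels from a change contrast. The expectancy-by-time term is needed. With three time points the two terms use 1 + 2 = 3 degrees of freedom.

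**The case against.** The strongest reply is that nothing here is wrong. Randomisation balances expectancy on average, chance imbalance lies inside the confidence interval, and pain power is about 86% even after the full 15% loss. Covariates are often settled in an analysis plan, which is not shown, and the article does not say that its listed terms are exhaustive. The assumed correlation has no support in the document. All of this stands. It is why the point is a suggestion, and it lapses if an analysis plan already includes the covariate. What remains is that the article names the model terms and collects a legitimate baseline covariate without stating any use for it.

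It is also fair to say that all 86 patients had been randomised when the article was submitted, so this would be a late change. That limits when it can be made but does not rule it out.

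A reader might infer something stronger: that the trial presents blinded outcome measurement when participants who know their arm rate every analysed outcome, and that leaving out expectancy lets the resulting bias through. The first half of the factual premise is true: the envelopes tell participants their group, and the abstract speaks of evaluation by a blinded assessor. But the article claims only that the assessor is blinded, describes that person's role as eligibility and collection of outcomes, and states openly that participants cannot be blinded. Both arms are active Pilates, so the document gives neither direction nor size for a reporting bias. A score taken before allocation cannot carry beliefs about the assigned arm, so it could not remove such a bias (step 6).

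**Conclusion.** A minor improvement, not an error. The planned unadjusted comparison is valid. Adding expectancy with its time interaction would reduce residual variance by about 4 to 16%, and the standard error of the pain difference by about 2 to 8%. This assumes a correlation of 0.2 to 0.4 with change in outcome, 43 per arm, and an SD of change of 1.4. If expectancy relates mainly to the baseline level, the gain shrinks towards zero. The documents do not support a finding of bias from the omission or of misdescribed blinding.

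**What to change.** In Statistical analysis, before the group codes are broken and preferably before any comparison of the coded groups is run:

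- add the pre-randomisation expectancy score and its interaction with time as fixed covariates in each outcome model;
- keep the credibility score out of these models, because it is measured after allocation, and report it by arm;
- keep the model with treatment, time and their interaction as a sensitivity analysis.

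The cost is a few sentences and about three degrees of freedom. No new data are needed, since the score is already part of the baseline assessment.

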### Statistical analysis

Data will be double-entered. The statistical analysis will be performed on an intention-to-treat basis. The effects of the intervention on pain intensity, global impression of recovery, general and specific disability, and kinesiophobia will be calculated using linear mixed models [33], which will incorporate terms for treatment, time, and treatment by time interactions (these interaction terms are equivalent to the between-group differences adjusted for the baseline estimates). The level of significance will be set at α=0.05. The data will be analyzed using the SPSS 19 for Windows by a blinded statistician who will receive coded data.

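### The treatment-by-time terms described as baseline-adjusted are differences in change from baseline: unbiased, but less precise than true baseline adjustment and open to misreading

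*Protocol article*

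**What the plan says.** The Statistical analysis section plans linear mixed models for pain, global impression of recovery, general and specific disability, and kinesiophobia, "which will incorporate terms for treatment, time, and treatment by time interactions". A bracketed remark then interprets the model: "these interaction terms are equivalent to the between-group differences adjusted for the baseline estimates".

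The time points are set under Procedures: "Outcomes will be collected at baseline, six weeks and six months after randomisation". The Abstract confirms that all these outcomes, including global perceived effect, are assessed before randomisation as well as at both follow-ups. The article mentions neither a baseline covariate nor a baseline mean shared by the arms.

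Three other statements bear on the point:
- Sample calculation: "A correlation of r=0.50 between the follow-up assessments within the outcome measurement was assumed in these calculations". No baseline-to-follow-up correlation is given.
- Procedures: "A simple randomization schedule was performed using Microsoft Excel for Windows". No blocking or stratification is described.
- Secondary outcomes, on the Global Perceived Effect Scale: "This scale compares the onset of symptoms to the last few days".

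**The concern.** To most trial readers, a difference adjusted for baseline means an analysis-of-covariance estimate, that is, a comparison of follow-up scores at equal baseline values. The stated model does not produce that. Its treatment main effect gives each arm its own baseline mean, so each interaction is the follow-up difference minus the full baseline difference.

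Two things are at stake. The results paper could carry over a description that readers will misunderstand. And the chosen contrast has a larger standard error than an adjusted one from the same data. It also moves against any chance baseline imbalance, which simple randomisation of 86 people allows. Global perceived effect fits least well: the scale already rates change since onset, so the interaction becomes a change in a change rating.

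**Working it through.** **Inputs from the Sample calculation section.** Pain: 1 point, SD 1.4. Roland-Morris: 4 points, SD 4.9. Global perceived effect: 1 point, SD 1.3. Alpha 0.05, power 80%, loss up to 15%, N = 86.

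**Assumptions, not in the document.** Two-sided test; equal arms; the same SD at baseline and follow-up; baseline-to-follow-up correlation r, shown over a range.

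**The plan's own figure.** For pain, n per arm = 2 × (1.96 + 0.84)² × 1.4² / 1² = 30.8, so 31, or 62 in total and 73 after 15% loss (up to 75 with a t-based formula or other rounding). Power of about 85% gives 36 per arm, 43 after loss, which is 86. The stated 86 is therefore larger than its 80% inputs need. That is a separate matter, but it gives the planned contrast some slack.

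**Step 1: what the interaction estimates.** Let D0 be the between-arm difference in baseline means and Dk the difference at follow-up k.
- Stated model: interaction at k = Dk − D0.
- Baseline-adjusted difference: Dk − b × D0, where b is the regression slope of follow-up on baseline. With equal SDs, b = r.

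The two agree only if b = 1. As a check, the stated model was fitted to simulated complete data. Its interactions (0.0625 and −0.1151) equalled the differences in mean change exactly.

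If instead only the two follow-ups were modelled, the interaction would compare the six-month effect with the six-week effect and would involve no baseline at all. The bracketed remark makes sense only with baseline as a time level.

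**Step 2: variance.** Multiply each factor by SD² × (1/n1 + 1/n2).
- Change contrast: 2(1 − r).
- Baseline-adjusted: 1 − r².
- Ratio: 2/(1 + r), above 1 for every r < 1.

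| r | change | adjusted | ratio |
|---|---|---|---|
| 0.3 | 1.40 | 0.91 | 1.54 |
| 0.5 | 1.00 | 0.75 | 1.33 |
| 0.7 | 0.60 | 0.51 | 1.18 |

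At r = 0.5, √0.75 = 0.87, so adjusted intervals are 13% narrower. In 20,000 simulated trials (43 per arm, SD 1.4, r = 0.5) the standard errors were 0.301 and 0.262, a variance ratio of 1.32.

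**Step 3: power for pain (noncentral t).** Planned loss: 0.85 × 86 = 73 completers, 36 and 37 per arm. The Discussion reports two losses so far at six months; 86 − 2 = 84 gives about 42 per arm.

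| r | 36/37: change | 36/37: adjusted | 42/42: change | 42/42: adjusted |
|---|---|---|---|---|
| 0.3 | 72% | 88% | 78% | 92% |
| 0.5 | 85% | 93% | 90% | 96% |
| 0.7 | 97% | 99% | – | – |

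At r = 0.4 the planned contrast has 78.5% with 36/37 (79.6% by the normal approximation) and 84% with 42 per arm. For Roland-Morris it has 83% at r = 0.3 and 93% at r = 0.5 with 36/37.

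**Step 4: chance imbalance.** Given a baseline gap D0, the change contrast shifts by −(1 − r) × D0. The standard error of the baseline difference in pain is 1.4 × √(2/43) = 0.30. At r = 0.5 a one-SE gap moves the estimate by 0.5 × 0.30 = 0.15 point. In the simulation the contrast correlated −0.50 with the baseline gap; the adjusted estimate correlated about 0.

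**Step 5: global perceived effect.** Ignoring baseline has variance factor 1, and 2(1 − r) exceeds 1 when r < 0.5. At r = 0.2 with 36/37, power is 73% for the change contrast, 91% adjusted and 90% ignoring baseline.

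**The case against.** The best defence is that the bracketed sentence can be read as true. It speaks of baseline estimates, not of a baseline covariate, and in this model those could be the arms' estimated baseline means, which the interaction does subtract. This stands in part: the sentence is ambiguous rather than plainly false. It does not remove the loss of precision, which is the same on either reading.

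Second, a treatment-by-time mixed model is a legitimate analysis. A reader might infer from talk of over-correction that the trial's estimate is biased or its test invalid. The documents do not support that. Allocation is random, so the change contrast is unbiased and keeps its type I error. The shift in Step 4 is conditional on the imbalance that happens to occur and averages to zero.

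Third, a reader might infer that the trial is underpowered. At r = 0.5 it is not: pain has 85% even after the full planned loss, and the losses reported in the Discussion are much lower. Roland-Morris, the other primary outcome, stays above 80% at r = 0.3. A shortfall arises only for pain among the two primaries, and only at low r.

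Fourth, large imbalances should not be used to illustrate the harm. A 1-point baseline gap in pain would be 1/0.30, or about 3.3 standard errors.

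Finally, an unseen analysis plan might specify a baseline covariate. Even so, the article itself states this model and this interpretation, and the sentence would still need correcting.

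**Conclusion.** The point holds as one of wording and efficiency. As written, the interactions are differences in change from baseline, not differences conditional on baseline, and the sentence is likely to be taken for the latter. The cost is a variance 18% to 54% larger than that of a true baseline-adjusted difference for r from 0.7 to 0.3. For pain after 15% loss, that is a drop from 99% to 97% at one end and from 88% to 72% at the other.

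These sizes rest on the assumed r and on equal SDs and arm sizes. The stated 0.50 refers to follow-up assessments and cannot be taken as the baseline-to-follow-up value. The remark on global perceived effect likewise depends on an r below 0.5 that the article does not give, and concerns a secondary outcome. This should be fixed because the gain is essentially free, not because the planned result would be invalid.

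**What to change.** Before the treatment code is broken, choose one of two models and state it:

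- **Baseline as covariate.** Model the six-week and six-month scores with treatment, time, treatment-by-time, baseline score and baseline-by-time.
- **Shared baseline mean.** Keep baseline as an outcome, drop the treatment main effect so that both arms have one baseline mean, and retain the treatment-by-time terms at the two follow-ups.

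In either case, report the treatment difference at each follow-up and reword the bracketed sentence to match. If the stated model is kept, call the terms differences in change from baseline and drop the claim of baseline adjustment.

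The cost is a few lines of plan text and SPSS mixed-model syntax. No new data or patients are needed. When the article was submitted, 78 participants had completed the six-month follow-up, and the statistician is to receive coded data, so the change could be made without knowledge of the results by arm.
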